**Methods and analysis:**

This longitudinal between-subjects study will recruit 60 participants who will each be randomly assigned to receive either active or sham tDCS. Participants will undergo 5 sessions, each spaced approximately one week apart. In session, they will receive 20 minutes of (active/sham) 1.5mA anodal stimulation over the right dorsolateral prefrontal cortex while receiving training in cognitive reappraisal. Primary outcomes include changes in cannabis use during the study, changes in electroencephalogram brain activity when viewing cannabis cues, and changes in cannabis craving intensity.

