The present study seeks to evaluate the efficacy of tDCS to the right dlPFC paired with training in cognitive reappraisal in improving craving regulation and reducing cannabis use in individuals with CUD. Specifically, we hypothesize that participants who receive active versus sham tDCS will have 1) greater reductions in daily cannabis use, 2) changes in neural correlates of EEG features associated with craving (e.g., relatively diminished LPP amplitude and increased delta power) while viewing cannabis cues, and 3) greater reductions in cannabis craving. We also hypothesize tDCS-related increases in neural correlates of EEG features associated with regulation (e.g., frontal theta power).

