## Materials and methods

### Study design

This protocol is written in accordance with the Standard Protocol Items: Recommendations for Interventional Trials (SPIRIT) reporting template [36]. The present study will utilize a randomized design where participants are allocated to either an active stimulation condition or a sham control condition in a 1:1 ratio. To ensure randomization of active/sham administration across sexes, this 1:1 ratio is allocated within males and females separately. To minimize bias, both study participants and research staff running study visits will be blinded to the participant’s assigned experimental condition. This entails five weekly visits (baseline and four weekly visits thereafter), during which participants will undergo a 20-minute session of (active/sham) tDCS and reappraisal training each week. Participants will complete a self-report measure of cannabis craving [37] immediately before and after each tDCS and reappraisal training session. Before the first tDCS session on the first visit and after the last tDCS session on the fifth visit, participants will complete the Regulation of Craving (ROC) task [3,38], during which EEG activity will be recorded. In addition to the in-person study visits, beginning after the first study visit and ending at the last visit, participants will provide information on past 24-hour cannabis use through a daily survey delivered via short message services (SMS).

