### Primary outcomes

The first primary outcome is cannabis use during the study. This will be measured through a brief daily survey. Participants will be sent a link to a REDCap survey at 8:00am daily to report on cannabis use over the last 24 hours. Participants will be asked about the amount of cannabis used, the form of cannabis used (e.g., smoked, vaped), and how the amount used compares to their typical use amount on a 5-point Likert scale, where 1 indicates much less cannabis used than usual, 3 indicates the usual amount of cannabis was used, and 5 indicates much more cannabis used than usual.

The second primary outcome is the EEG correlates of craving and regulation during the ROC task (Fig 2), which participants will complete before the first intervention session and after the fifth intervention session. The ROC task utilizes E-Prime software to present participants with a series of validated cannabis images, including pictures of the cannabis plant and images depicting various cannabis primary use methods [51]. The ROC task consists of 25 LOOK and 25 NEGATIVE trials total, presented in alternating LOOK and NEGATIVE blocks of 5 trials each (i.e., 5 LOOK trials, followed by 5 NEGATIVE trials, followed by 5 LOOK trials, etc.). During the LOOK trials, participants will be instructed to simply look at the image; during the NEGATIVE trials, participants will be instructed to think about the negative consequences of using cannabis. EEG data will be collected using a 128-lead Electrical Geodesic EEG system, with gel-based collection, sampled at 1000 Hz.

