### Data analysis

Data collected throughout this study will primarily be analyzed using SPSS software. To address the first aim of the study, reductions in cannabis use, as reported by research participants through the daily-administered REDCap surveys, will be analyzed using a multilevel modeling strategy. Multilevel modeling with maximum likelihood estimation for missing data will be used to conduct a linear analysis of daily use of cannabis using a nested hierarchical structure with both between- and within-subject predictors. The main effects of Group (i.e., stimulation versus sham) and Time, as well as the Group x Time interaction will be the primary fixed effects of interest. Daily use of cannabis will be compared across the study weeks, and multilevel models will be constructed to examine the slopes of longitudinal data across the weeks.

Statistical analysis of the EEG correlates of craving and regulation will be conducted using Netstation pipelines for ERPs and Matlab scripts for oscillatory power. Data will be filtered offline at 0.1–30 Hz. Ocular artifact correction will be performed on the mean amplitudes of each component with a specified timeframe. The components of interest for this analysis will consist of the P300, the LPP, and frontal theta power. These variables will be compared across Group (i.e., stimulation versus sham), Condition (i.e., LOOK or NEGATIVE), and Time (V1 and V5) in a series of ANOVAs. We hypothesize that active stimulation will result in heightened amplitude of the early LPP in the LATER condition, as regulation of craving is hypothesized to be enhanced, and diminished amplitude of the late LPP in the LATER condition, as arousal related to craving is hypothesized to be reduced. Further, we expect that frontal theta power will be enhanced after tDCS stimulation during the LATER condition.

For the third primary outcome, craving will be measured both pre- and post-tDCS using the MCQ [37], and active and sham groups will be compared via an ANOVA (Group x Condition x Time). Additionally, self-reported cravings elicited by cannabis images in the ROC task in both the LOOK and NEGATIVE conditions are rated on a 5-point Likert scale at baseline and post-treatment. These data will be averaged across trials and compared between groups via an ANOVA (Group x Condition x Time).

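### For the EEG measures and the ROC craving rating, V1 enters as a level of Time rather than as a covariate, which costs precision, and the deciding ANOVA term is not named

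*Protocol article*

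**What the plan says.** **Design.** The Abstract gives the size: "This longitudinal between-subjects study will recruit 60 participants who will each be randomly assigned to receive either active or sham tDCS". Under Study design, "participants are allocated to either an active stimulation condition or a sham control condition in a 1:1 ratio", and this is done within each sex. The Primary outcomes section describes the ROC task with EEG as one "which participants will complete before the first intervention session and after the fifth intervention session". V1 is therefore a true pre-treatment value and V5 the only post-treatment value.

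**Analysis.** Under Data analysis, P300, LPP and frontal theta are compared across Group, "Condition (i.e., LOOK or NEGATIVE), and Time (V1 and V5) in a series of ANOVAs". For the ROC rating: "These data will be averaged across trials and compared between groups via an ANOVA (Group x Condition x Time"). V1 is not named as a covariate for either. For daily cannabis use the same section names the fixed effects of interest, including Group x Time. It has no matching sentence for EEG or ROC craving.

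**Hypotheses.** The Introduction expects active versus sham differences, "relatively diminished LPP amplitude and increased delta power) while viewing cannabis cues, and 3) greater reductions in cannabis craving", with no contrast between task conditions. Data analysis places the EEG effects in one condition: "active stimulation will result in heightened amplitude of the early LPP in the LATER condition", and "we expect that frontal theta power will be enhanced after tDCS stimulation during the LATER condition". The task described under Primary outcomes has only LOOK and NEGATIVE trials.

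**The concern.** Two things are at stake.

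1. **Precision.** In a randomised trial with one value before and one after treatment, entering Time as a factor ties the between-group test to the raw change. Adjusting V5 for V1 estimates the same treatment difference with a smaller error and uses data already collected. With 60 participants and results meant to inform a larger trial, the lost precision carries forward into the estimates.

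2. **Target.** A three-factor ANOVA offers several terms involving Group, and they answer different questions. The hypotheses in the Introduction point to Group x Time. Those in Data analysis point to an effect within one condition. Without a named deciding term, a real effect could be judged by a term that cannot show it.

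**Working it through.** The protocol gives no power calculation, effect size, SD, alpha or V1-V5 correlation, so there is no figure to reproduce.

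**Inputs from the protocol:** 60 participants, 1:1, so 30 per arm; one V1 and one V5 value.

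**Assumptions:** two-sided alpha 0.05, effect 0.5 SD, no dropout, equal SD s at V1 and V5, V1-V5 correlation rho from 0.3 to 0.9. Power is from the noncentral t with 58 df (change) or 57 df (ANCOVA).

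**Step 1: precision for one measure in one condition.**
- Change score: variance per person = 2(1-rho)s².
- V5 adjusted for V1: variance per person = (1-rho²)s².
- Ratio = (1-rho²)/[2(1-rho)] = (1+rho)/2.
- Standard error of the group difference = sqrt(variance x 2/30).

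| rho | Change variance (s²) | ANCOVA variance (s²) | Ratio | N for ANCOVA to match 60 on change | Power, change | Power, ANCOVA |
|---|---|---|---|---|---|---|
| 0.3 | 1.40 | 0.91 | 0.65 | 39 | 36% | 51% |
| 0.5 | 1.00 | 0.75 | 0.75 | 45 | 48% | 59% |
| 0.7 | 0.60 | 0.51 | 0.85 | 51 | 69% | 76% |
| 0.9 | 0.20 | 0.19 | 0.95 | 57 | 99% | 99% |

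A simulation of 10,000 trials at each of rho 0.3, 0.5 and 0.7 found both estimators unbiased. The variance ratios were 0.68, 0.77 and 0.87, slightly above theory because the slope is estimated. Power was 36% vs 51%, 48% vs 59% and 69% vs 75%.

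The direction does not depend on equal SDs. With SDs s1 and s5, change variance minus ANCOVA variance = (s1² + s5² - 2 rho s1 s5) - s5²(1-rho²) = (s1 - rho s5)², which is never negative.

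**Step 2: the planned ANOVA averages over LOOK and NEGATIVE.** Let rt be the correlation over time within a condition, rc between conditions at one visit, and rx across both. In units of s²:
- Group x Time on the condition mean: variance = (1-rt) + (rc-rx).
- ANCOVA on the condition mean: variance = m - c²/m, with m = (1+rc)/2 and c = (rt+rx)/2.
- Three-way contrast: variance = 4(1 - rt - rc + rx).

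At rt = 0.5, rc = 0.5, rx = 0.4:
- Group x Time = 0.5 + 0.1 = 0.60.
- m = 0.75 and c = 0.45, so ANCOVA on the mean = 0.75 - 0.2025/0.75 = 0.48.
- Three-way = 4 x 0.4 = 1.60.

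Power for 0.5 SD in **both** conditions:

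| rt / rc / rx | Planned Group x Time | ANCOVA, condition mean | ANCOVA, one condition | Three-way |
|---|---|---|---|---|
| 0.5 / 0.5 / 0.4 | 69% | 78% | 59% | 5% |
| 0.5 / 0.7 / 0.4 | 57% | 68% | 59% | 5% |
| 0.7 / 0.7 / 0.6 | 85% | 89% | 76% | 5% |

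The 5% is the type I error: with equal effects the three-way contrast is 0.5 - 0.5 = 0.

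**Step 3: effect of 0.5 SD in NEGATIVE only.** At the same three sets the three-way test has 33%, 57% and 57% power. ANCOVA within NEGATIVE has 59%, 59% and 76%. At 0.7 / 0.8 / 0.6 the order reverses: three-way variance = 4 x 0.1 = 0.40 and power 85%, against 76%.

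**Step 4: Group main effect.** It averages an expected difference of 0 at V1 with the effect at V5: (0 + 0.5)/2 = 0.25 SD, half the effect.

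**The case against.** **The plan does not make the three-way interaction the test.** A reader might infer from the notation Group x Condition x Time that it does, and so that the trial is bound to miss a uniform benefit. The text does not support this. It lists the ANOVA factors, and the same model contains Group x Time, which tests the reduction in craving directly. Step 2 gives that term 57% to 85% power for a uniform effect under the sets tabulated. What stands is narrower: the deciding term is not named.

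**The Condition contrast is not irrelevant.** Data analysis places the LPP and theta effects in one condition, and ROC ratings are averaged separately by condition and compared. Step 3 shows that the three-way term can be informative for such an effect. This objection stands.

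**Adjusting within a single condition is not always a gain.** For a uniform effect, the planned condition-averaged Group x Time can beat a single-condition ANCOVA (69% against 59% at 0.5 / 0.5 / 0.4). This also stands, and it is why the ROC fix below uses the condition mean.

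**It is only efficiency, and a condensed article may leave detail to a fuller plan.** Both analyses are valid, and the gain is 5% of variance at rho 0.9. A fuller plan may name the deciding term. But the article itself fixes Time as a factor, and its own hypotheses point to different terms and to a condition that the task does not contain.

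**Conclusion.** The point holds as lost precision and an unfixed target, not as bias or an invalid test. For the EEG measures and the ROC rating, adjusting V5 for V1 cuts the variance of the treatment estimate by 35%, 25%, 15% or 5% at assumed correlations of 0.3, 0.5, 0.7 or 0.9, before the small cost of estimating the slope. On the LOOK/NEGATIVE mean, under the assumed sets tabulated, power for 0.5 SD rises by about 4 to 11 percentage points over the planned Group x Time. All sizes rest on correlations and an effect that the protocol does not give; the direction does not.

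It would also be too strong to say that two of the three primary outcomes are affected in full. The third outcome includes the MCQ, which is taken before and after each of five sessions and is outside this point. The change is worth making; the article reports that recruitment and data collection had not begun.

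**What to change.** - **All EEG measures and the ROC rating:** replace Time as a factor with an ANCOVA of the V5 value on Group, the V1 value of the same measure, and sex (the stratification factor). The Group coefficient is the deciding term.
- **ROC craving:** take the mean of LOOK and NEGATIVE as the primary variable, at both V1 and V5.
- **LPP and frontal theta:** test Group within the condition that the hypothesis names. First reconcile LATER in Data analysis with the task's LOOK and NEGATIVE conditions.
- **Secondary:** keep Group x Condition at V5, adjusted for V1, as a separate named contrast. An example is the NEGATIVE-minus-LOOK difference at V5 regressed on Group, the same difference at V1, and sex.

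The cost is analysis wording and one or two degrees of freedom. V1 values and sex are already collected.

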**Fig 2 pone.0328205.g002:**
[figure not shown]
Schematic representation of a single trial of the ROC task. Participants will view a fixation cross for 3 seconds before the instruction (LOOK/NEGATIVE) for participants is displayed for 3 seconds. A cannabis image will be displayed for 6 seconds, during which participants are to either look at the image (“LOOK”) or think about the negative consequences of using cannabis (“NEGATIVE”). After a 3-second fixation cross, participants will have up to 10 seconds to rate their level of craving for cannabis on a 5-point scale. Participants will complete 50 trials, comprising 25 LOOK trials and 25 NEGATIVE trials.

Our rationale for ERP component selection and labeling is grounded in the literature on emotional image processing. In picture-viewing paradigms involving affectively salient stimuli, the early neural response often overlaps with the P300 in both timing and topography. However, unlike discrete stimuli used in tasks like oddball tasks, emotional images typically evoke more complex and variable cognitive appraisal processes, leading to temporal jitter in the onset of peak neural engagement across trials. This results in a less sharply defined P300 and the emergence of a sustained slow-wave positivity that blends with the LPP over centro-parietal regions. To align with conventions in the ERP literature, we assess the P300 in the ~ 250–300 ms window and the LPP in the 600–900 ms window. Thus, mean amplitudes of the P300 (~250–300 ms following cannabis cue) and the early LPP (600–900 ms following cannabis cue) will be quantified. Additional analysis will also assess and consider frontal theta power.

The third primary outcome is self-reported levels of cannabis craving. This will be assessed using the MCQ [37], which will be administered immediately before and after each tDCS and reappraisal training session at each study visit. It will also be assessed using the ROC task on V1 and V5: self-reported levels of craving in response to cannabis images will be averaged separately across all LOOK trials and all NEGATIVE trials and compared.

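### The EEG analysis predicts a smaller late LPP as the sign of reduced craving arousal, but the only LPP window that the plan scores is 600–900 ms, which it calls early

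*Protocol article*

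**What the plan says.** The second primary outcome is the set of EEG correlates of craving and regulation during the Regulation of Craving (ROC) task, recorded before the first intervention session and after the fifth.

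**Scoring (Protocol article, Primary outcomes, text after the Fig 2 legend).** The windows are given in milliseconds: "we assess the P300 in the ~ 250–300 ms window and the LPP in the 600–900 ms window". The next sentence names the LPP measure: "the early LPP (600–900 ms following cannabis cue) will be quantified". The Fig 2 legend gives the exposure: "A cannabis image will be displayed for 6 seconds".

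**Hypotheses (Data analysis).** Three directional predictions are made for active stimulation:
- "heightened amplitude of the early LPP in the LATER condition, as regulation of craving is hypothesized to be enhanced"
- "diminished amplitude of the late LPP in the LATER condition, as arousal related to craving is hypothesized to be reduced"
- "frontal theta power will be enhanced after tDCS stimulation during the LATER condition"

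**Components analysed (Data analysis).** "The components of interest for this analysis will consist of the P300, the LPP, and frontal theta power". They are compared by Group, Condition (LOOK or NEGATIVE) and Time in a series of ANOVAs.

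**Hypotheses (end of Introduction).** The EEG features tied to craving are given as "relatively diminished LPP amplitude and increased delta power", with no early or late qualifier. Frontal theta is named there as a regulation feature.

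**The concern.** Data analysis treats the early and late LPP as two measures with opposite predicted signs and different meanings: regulation goes up, craving arousal goes down. The scoring rule supplies a number for the first only. If the plan is followed exactly, the second primary outcome yields no result on the prediction that links brain activity to reduced craving.

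Two things could follow. The prediction may go untested and unreported. Or someone may choose a late window at analysis, when nothing in the article limits where it should lie. A related difficulty is that the single scored LPP window carries two predicted directions in different sections. A fall could be read as less craving under the Introduction, and a rise as better regulation under Data analysis.

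**Working it through.** The plan gives no figure to reproduce. The check sets the predictions against what is scored.

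| Prediction | Where stated | Meaning given | Scored under the plan? |
|---|---|---|---|
| Early LPP rises | Data analysis | Regulation | Yes, 600–900 ms |
| Late LPP falls | Data analysis | Craving arousal | No window defined |
| Frontal theta rises | Data analysis | Regulation (so classed in the Introduction) | Listed as a component |
| LPP falls, early or late not stated | Introduction | Craving | Only at 600–900 ms, where Data analysis predicts a rise |
| Delta power rises | Introduction | Craving | Not among the listed components |

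1. **Windows.** Two ERP windows are stated: about 250–300 ms (P300) and 600–900 ms (LPP, labelled early). The number of late-LPP windows is 0. The general term LPP in the component list adds none, because the only time range attached to it is 600–900 ms.

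2. **Could the Introduction supply the craving measure?** Its diminished LPP could be tested at 600–900 ms, but Data analysis predicts the opposite sign there. Its delta power is not in the component list. Neither route gives a craving measure that agrees with the rest of the plan.

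3. **Are the data available?** EEG is recorded during the ROC task and the image lasts 6 s. Time after the scored window: 6.0 − 0.9 = 5.1 s per trial. A late window can be extracted from recordings that will exist anyway.

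4. **Condition.** All three Data analysis predictions are placed in a LATER condition. The task and the ANOVA have LOOK and NEGATIVE only, so a late window alone would not make the prediction testable as worded.

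5. **Illustration only: a window chosen after the data are seen.** Nothing in the article says this will happen. Assume five windows of about 1 s in the 5.1 s, each tested at two-sided 5%, with success counted only for a decrease (nominal 2.5% per window). If the windows were independent, the chance of at least one false confirmation is 1 − 0.975⁵ = 11.9%. With equal correlation r between windows (assumed), the chance is 1 − ∫ φ(z) Φ[(1.96 − √r·z)/√(1 − r)]⁵ dz. This gives about 9% at r = 0.5, 7.4% at r = 0.7 and 6.4% at r = 0.8. The range is about 6–12% against 2.5%. The number of windows and the correlations are assumptions, and the defect does not depend on them.

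**The case against.** **A fuller document may define the window.** A journal article condenses, and exact ERP windows often sit in a full protocol or analysis plan. This carries limited weight. The article does not leave windows open: it argues for its choice, states limits in milliseconds and says which amplitudes will be quantified. A late window elsewhere would still have to be reconciled with this text.

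**The sentence may be carried over from another task.** The reference to a LATER condition suggests that the hypotheses were written for a different version of the task. That is an inference, but a reasonable one. It bears on the remedy: rewriting or deleting the hypotheses may be more natural than adding a window.

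**The consequence is limited.** This is a pilot. Craving is also a separate primary outcome, measured by the Marijuana Craving Questionnaire and the ROC ratings. This stands, and it confines the point to the EEG outcome.

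**Stronger readings a reader might infer.**
- That the late-LPP data are lost or discarded. They are not: the EEG is recorded, and the late part is unscored.
- That the article as a whole has only one EEG prediction about craving. That is true of Data analysis only, since the Introduction names two others.
- That the false-positive rate of a primary outcome is inflated. The documents do not support this, because no post-hoc choice of window is planned. Counting significance in either direction would also overstate the chance of falsely confirming a prediction that has a stated sign.

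**Conclusion.** The point holds as a contradiction between a stated hypothesis and a stated scoring rule. One of the three directional EEG predictions in Data analysis, and the only one of the three tied to reduced craving, has no measure under the plan as written. The Introduction does not repair this and adds a conflict of direction in the one window that is scored. The conclusion rests on the text alone and on no numerical assumption.

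It should be corrected, but it does not threaten the trial. It touches one mechanistic prediction within one of three primary outcomes, and the self-reported craving results do not depend on it.

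**What to change.** Before the data are seen, take one of two routes:

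- **Score it.** Add one fixed late-LPP window to Primary outcomes, starting after 900 ms and ending within the 6 s image, as mean amplitude at the same sites as the early LPP. List it among the components in Data analysis with its predicted decrease.
- **Withdraw it.** Delete the late-LPP hypothesis and state that the ERP analysis makes no claim about craving arousal.

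Under either route, make two further corrections in the same edit. State the EEG predictions for conditions that the task contains (LOOK and NEGATIVE) in place of LATER. Make the predicted LPP direction in the Introduction agree with Data analysis, naming the window each prediction refers to.

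The first route costs one scoring window on EEG that is recorded anyway and one more EEG measure in the outcome family. The second costs a few lines of text. Neither needs extra visits, participants or recordings. Study status says that recruitment and data collection have not begun, with recruitment expected from April 2025. If collection has since started, the change is still sound provided that it is dated and made before EEG results by group are examined.

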At the start of each visit, the study team will collect biological verification of tetrahydrocannabinol (THC) through urine and salivary toxicology screening. Urine toxicology screening will be completed at each visit to ensure participants meet the full inclusion criteria for the study, in that participants need to both test positive for the presence of THC and negative for exclusionary substances (e.g., opioids, cocaine, methamphetamine). Salivary toxicology screening will be completed at the start of each study visit to ensure that participants abstain from cannabis use prior to each study appointment (i.e., as demonstrated by THC concentration of ≤10 ng/ml). Participants with a positive salivary toxicology screen will be asked to reschedule their visit for another day.

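### The MCQ craving outcome, measured at five visits, is assigned an ANOVA that drops incomplete participants or leaves visits unused, although a likelihood mixed model is already planned for daily use.

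*Protocol article*

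**What the plan says.** The Data analysis section assigns one method to each primary outcome.

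- **Daily cannabis use:** "Multilevel modeling with maximum likelihood estimation for missing data will be used to conduct a linear analysis of daily use of cannabis". This is the only place where missing data are mentioned.
- **EEG components:** compared across Group, Condition "and Time (V1 and V5) in a series of ANOVAs".
- **MCQ craving:** "active and sham groups will be compared via an ANOVA (Group x Condition x Time").
- **ROC craving ratings:** "These data will be averaged across trials and compared between groups via an ANOVA (Group x Condition x Time"), at baseline and post-treatment.

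Under Primary outcomes, the MCQ is an instrument "which will be administered immediately before and after each tDCS and reappraisal training session at each study visit". Five visits therefore give ten scores per participant. The ROC task with EEG is done twice, at V1 and V5. SPSS is named as the main software. The article does not say which visits are the levels of Time for the MCQ. Nor does it say what Condition means for a questionnaire that has no LOOK or NEGATIVE trials.

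**The concern.** Time varies within participants for the MCQ, EEG and ROC outcomes, and Condition does so for EEG and ROC. The natural reading of these ANOVAs is therefore the mixed-design repeated-measures form. In its classical form, which is the SPSS default, a participant contributes only if every level entered is present.

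This matters most for the MCQ, the visit-based outcome with the most repeated measurements. One missed visit could remove up to four visits of observed scores, or the middle visits might not be used at all. The daily-use model would meanwhile keep everyone with any survey. In a trial of 60, the three primary outcomes could then describe different groups of people.

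Some missing data are foreseeable. Under Participant timeline, anyone reporting a serious adverse event is withdrawn. Under Eligibility criteria, toxicology is rechecked at every visit. Under Data monitoring, retention and availability of primary outcome data are reviewed at least monthly.

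**Working it through.** **Inputs from the article.** "This longitudinal between-subjects study will recruit 60 participants", allocated to an "active stimulation condition or a sham control condition in a 1:1 ratio", so 30 per arm. There are five visits. The MCQ is taken at all five; EEG and ROC craving are taken at V1 and V5.

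**Inputs assumed.** The article gives no dropout rate, effect size, alpha or power, so there is no planned figure to reproduce. Let m be the chance of missing each visit after V1, independent across visits, with range 3% to 15%. V1 is taken as complete.

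**Participants kept by a complete-case ANOVA.**

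- All five visits in Time: 60 × (1 − m)^4
- V1 and V5 only: 60 × (1 − m)

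For m = 5%: 60 × 0.8145 = 48.9, and 60 × 0.95 = 57. For m = 10%: 60 × 0.6561 = 39.4, and 60 × 0.90 = 54.

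**What that means for precision.** As an illustration only, take a two-sided alpha of 0.05 and a standardised difference d = 0.74, both assumed. With n per arm, power = Φ(d × √(n/2) − 1.96). With all 60, this is Φ(0.74 × √15 − 1.96) = Φ(0.906) = 82%.

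| m | N kept, five visits | Power | N kept, V1 and V5 | Power |
|---|---|---|---|---|
| 3% | 53 | 77% | 58 | 81% |
| 5% | 49 | 73% | 57 | 80% |
| 10% | 39 | 64% | 54 | 78% |
| 15% | 31 | 54% | 51 | 75% |

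These are simple two-group comparisons at the reduced N. They show what the lost participants cost, not the power of the planned ANOVA. For the MCQ, the V1-and-V5 columns also leave out V2 to V4: three of five visits, or six of ten scores.

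**Is there bias?** Simulations of the V1-to-V5 group difference in change, with a true value of −0.50 SD (negative favours active) and dropout depending on earlier observed scores, gave these completer estimates:

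- Same dropout rule in both arms, driven by the last craving level, 81% and 84% retained: −0.50, so no bias.
- Dropout rules that differ by arm, 62% to 73% retained: −0.53 and −0.57, so the effect is overstated by 0.03 to 0.07 SD. A likelihood-type estimate stayed at −0.50.
- Dropout rising with lack of improvement since V1, 61% to 78% retained: −0.47 to −0.44, so the effect is understated by 0.03 to 0.06 SD.

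The sign of the bias follows the dropout mechanism assumed, and the article does not fix that mechanism.

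**The case against.** **The ANOVAs do not delete everyone who misses a visit.** A reader might infer that they do. For EEG and ROC craving this is wrong: only V1 and V5 enter, so missing V2, V3 or V4 removes nobody. For the MCQ it is true only if all five visits are levels of Time, which the article does not state.

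**The bias need not be toward no effect.** A reader might reason that people who cannot abstain will miss visits, since saliva THC must be at or below 10 ng/ml. But the article says "Participants with a positive salivary toxicology screen will be asked to reschedule their visit for another day", so such a visit is delayed, not necessarily lost. The same section requires urine to be THC positive at each visit, which could instead affect people who have stopped using. The direction is open.

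**A large power loss is not established.** Deleting anyone who misses any of five visits and then testing only the V1-to-V5 change would give one, but that mixes the two readings and matches neither. Heavy dropout is also not implied by the article, which pays a $75 bonus for completing all five visits.

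**Some of this is detail for an analysis plan.** Listwise deletion is inferred, not written, and an analysis plan that is not shown could add imputation. This limits the certainty. It does not remove the point: the article itself names the method, and the usual form of that method handles incomplete data poorly, while a better one is already planned for another primary outcome.

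**A mixed model gains little for EEG and ROC craving.** This stands. Participants without V5 contribute only V1. Imputing V5 EEG amplitudes from craving and use scores needs correlations that the article does not give.

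**Conclusion.** The point holds, mainly for the MCQ. Under the classical ANOVA, either incomplete participants are removed (about 49 or 39 of 60 kept at an assumed 5% or 10% missed per visit, if all five visits enter), or the V2 to V4 scores go unused (if only V1 and V5 enter). For EEG and ROC craving the effect is small: about 57 or 54 of 60 kept at the same rates.

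The firm harms are lost precision, discarded MCQ scores and primary outcomes reported on different sets of participants. Bias is possible if missing visits depend on response, but the documents support no claim about its direction or size. The participant counts rest on assumed, independent missed-visit rates and on the default handling of incomplete data in a repeated-measures ANOVA. This is a worthwhile, inexpensive improvement to a pilot. It does not invalidate the design.

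**What to change.** **MCQ:** replace the ANOVA with the likelihood-based mixed model already planned for daily use (SPSS MIXED). Include all randomised participants and all available visits. Use Group, Visit, pre/post-session and their interactions as fixed effects, and read the group contrast at V5 from the model. This also settles what Time and Condition mean for the MCQ. Report the completer ANOVA as a sensitivity analysis.

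**EEG and ROC craving:** a mixed model with all available V1 and V5 data is enough. Imputation of missing V5 values can be an optional sensitivity analysis. For every outcome, report the number of participants analysed by arm.

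**Cost:** a change of wording in the Data analysis section and slightly more analysis work. No new data, visits or participants are needed. The mixed model assumes that data are missing at random given what was observed, and the plan should state this.
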